**Outline**

**0.1. Outline schema**

Patients undergoing an elective abdominal surgery (liver resection, pancreatoduodenectomy, or both) under general anesthesia

Informed consent

Registration

Data acquisition (operating room and intensive care unit)

Arterial blood pressure obtained by both noninvasive and invasive devices

Perfusion index (PI) derived from pulse oximeter

Estimating whether PI affects the agreement between the noninvasive and invasive arterial blood pressures

**0.2 Object and meaning**

ClearSight™ (Edwards Lifesciences Corporation, Irvine, CA USA) is a noninvasive monitor for measuring the arterial blood pressure, cardiac output, or other hemodynamic parameters. However, arterial blood pressure measured by the ClearSight is not reliable in critically ill patients or in those receiving vasopressors to maintain their blood pressure. It has been speculated that the unreliability may be due to reduced finger perfusion, but the evidence is lacking. The primary objective of this study is to assess whether the perfusion index (PI) affects the agreement between the arterial pressure measured by the ClearSight and the invasive arterial pressure.

**0.3. Selection of research subjects**

**Inclusion criteria**

(1) Aged ≥20 years

(2) Patients who are scheduled to undergo an elective major hepatectomy (defined as liver resection ≥ 3 segments), pancreatoduodenectomy, or both under general anesthesia.

(3) Cases with the indication for inserting an arterial catheter and for using the FloTrac system (Edwards Lifesciences).

(4) Patients with written informed consent for participation in this study.

**Exclusion criteria**

(1) Body weight <40 kg or >180 kg, body mass index >35 kg/m^2^.

(2) Patients with a pronounced disturbance of peripheral perfusion (Raynaud syndrome or peripheral artery occlusive disease).

(3) Patients with the presence of, or a known history of, arterial fibrillation.

(4) Patients with a known history of upper arm vascular surgery.

**0.4. Sample size and research period**

Estimated sample size: 30 cases

Research period: From the 19th of October 2016 to the 30th of September 2020

**0.5. Methods**

The arterial blood pressures measured by the ClearSight and the invasive arterial pressure are obtained in the operating room and the intensive care unit. The PIs are measured simultaneously with the measuring of the arterial pressures. In the analysis, all data are divided into two groups based on the PI value ≤1 / >1.

**Primary endpoint**

The standard deviation (SD) of the bias between arterial pressures measured with the ClearSight versus those measured with an arterial catheter.

**Analysis of the primary outcome**

Linear mixed-effects regression model (calculating the SD of the bias between the two devices)

Response variable: The mean differences between the two devices.

Covariate: Binarized PI (PI ≤1 and PI >1), heart rate, body temperature, the mean value of arterial pressure measured by the ClearSight (APcs), and the invasive arterial pressure.

Random effect: Subject

The model allows the variance of the bias to differ depending on the binarized PI.

Based on the results of this model, the ratio of the adjusted SD of bias is calculated.

If the PI value is determined to be an indicator of the agreement of the ClearSight and the invasive arterial pressure, it may be possible to judge the reliability of the APcs value in real time. Our study may beneficially contribute to patients by providing a minimally invasive solution.

0.6. **Lead principal investigator**

[name], Department of Anesthesiology and Critical Care Medicine, Yokohama City University Hospital

**1. Object and meaning**

ClearSight™ (Edwards Lifesciences Corporation, Irvine, CA USA) is a noninvasive monitor for measuring the arterial blood pressure, cardiac output (CO), or the other hemodynamic parameters such as stroke volume index (SVI), stroke volume variation (SVV), or systemic vascular resistance index (SVRI). With widespread use of the ClearSight, healthcare providers will be able to provide care in a less invasive manner.

The agreement between the arterial pressure values measured by the ClearSight (APcs) and the arterial catheter-based blood pressures (IAP) has been examined by several studies.[1-4] In patients undergoing cardiac surgery or those in the intensive care unit (ICU) after cardiac surgery, the APcs shows sufficiently good bias and precision to substitute for IAP. However, APcs is not reliable in critically ill patients or in those receiving vasopressors to maintain their blood pressure.[5-7] It has been speculated that the unreliability may be due to reduced finger perfusion from high peripheral vascular resistance, continuous vasopressor administration, and/or edema, but the evidence is lacking.

We hypothesized that lower peripheral perfusion would affect the agreement between the arterial APcs and the IAP. As an indicator of peripheral perfusion, we chose the perfusion index (PI) measured by pulse oximetry, which is calculated as the ratio of the pulsatile infrared signal to the non-pulsatile infrared signal in the peripheral tissue.[8] The PI can be obtained continuously and noninvasively, and lower values indicate peripheral hypoperfusion or vasoconstriction.

The primary objective of this study is to assess whether the PI affects the agreement between APcs and IAP. The secondary objective of this study is to assess whether the PI affects the agreement between cardiac output, SVI, SVV, or SVRI as measured by the ClearSight and those measured by the FloTrac system (Edwards Lifesciences Corporation, Irvine, CA USA). If the PI value is determined to be an indicator of the agreement of the ClearSight and the invasive arterial pressure, it may be possible to judge the reliability of the APcs value in real time. Our study may beneficially contribute to patients by providing a minimally invasive solution.

**2. Evidence of scientific rationality of research**

**2.1. Explanation of target disease**

The primary objective of this study is to assess whether the PI affects the agreement between the APcs and the IAP in the perioperative setting. If it can be determined that the PI is a real time index of the reliability of the ClearSight, this monitor may safely be used more widely in daily clinical practice.

Our study will require the participants to be using the ClearSight, an arterial catheter, and the FloTrac at same time. Therefore, we are targeting patients who are scheduled to undergo an elective major hepatectomy (defined as liver resection ≥ 3 segments), pancreatoduodenectomy, or both under general anesthesia, because the radial artery catheter placement and the use of the FloTrac system are planned for every one of these patients out of clinical necessity. The reasons are as follows: First, to avoid an unnecessary procedure for the subjects, and to reduce the burden on them as patients. Second, since intraoperative vasoconstriction occurs in operations that are large, invasive, and long, low PI values may be collected more frequently in these patients.

**2.2. Current status of treatment**

In our clinical setting, the placement of the arterial catheter and the use of the FloTrac are routinely performed for elective major hepatectomy, pancreatoduodenectomy, or both under general anesthesia. These operations are large, invasive, and long, and there is a need to manage the hemodynamics and the fluid balance strictly.

**2.3. Explanation of research**

In patients undergoing cardiac surgery or those in the ICU after cardiac surgery, the APcs shows sufficiently good bias and precision to substitute for IAP. However, APcs is not reliable in critically ill patients or in those receiving vasopressors to maintain their blood pressure. There is no report which has researched the real time index of the agreement of the IAP and the APcs with the ClearSight.

The protocol of this study is constructed based on the past similar studies which examined the agreement between the APcs and the IAP.

**3. Equipment information**

(1) EV1000 monitor, ClearSight finger cuff (Edwards Lifesciences Corporation, Irvine, CA USA)

This monitor system can noninvasively measure the arterial blood pressure by the cuff attached the subject’s finger without an invasive procedure such as the insertion of a catheter into the artery.

(2) FloTrac™ system (Edwards Lifesciences): Extracorporeal continuous cardiac output monitor

Based on the arterial pressure waveform from the transducer which is attached to a standard radial or femoral arterial catheter, this system can measure some hemodynamic parameters such as stroke volume (SV) or CO. This monitor will be used as a reference for comparison of the reliability of arterial blood pressures or other hemodynamic parameters measured by the ClearSight.

(3) Radical-7^®^ pulse oximeter (Masimo Corp., Irvine, CA USA)

This monitor can noninvasively measure pulse rate, peripheral oxygen saturation (SpO_2_), and the PI value, and is standard equipment for anesthesia management.

The pulse oximeter measures SpO_2_ by using the several wavelengths. The PI is calculated as the ratio of the pulsatile infrared signal to the non-pulsatile infrared signal in the peripheral tissue. Therefore, the PI value means the peripheral perfusion or vascular tone at the measurement site. A low PI value indicates poor peripheral perfusion.

**4. Diagnostic criteria and stage / disease type / pathology classification**

Not applicable

**5. Policy for the selection of study subjects**

**5.1. Inclusion criteria**

(1) Aged ≥20 years

(2) Patients who are scheduled to undergo an elective major hepatectomy (defined as liver resection ≥ 3 segments), pancreatoduodenectomy, or both under general anesthesia.

(3) Cases with the indication for inserting an arterial catheter, and for using the FloTrac system.

(4) Patients with written informed consent for participation in this study.

**5.2. Exclusion criteria**

(1) Body weight <40 kg or >180 kg, and body mass index >35 kg/m^2^.

(2) Patients with a pronounced disturbance of peripheral perfusion (Raynaud syndrome or peripheral artery occlusive disease).

(3) Patients with the presence of, or a known history of, arterial fibrillation.

(4) Patients with a known history of upper arm vascular surgery.

**6. Procedure of study participation and case registration / assignment**

**6.1.** This study will be registered with the University hospital Medical Information Network Clinical Trials Registry [UMIN-CTR (http://www.umin.ac.jp/ctr/index-j.htm)] for information disclosure.

**6.2. Facility registration**

Not applicable

**6.3. Case registration**

First, patients are confirmed to meet the inclusion criteria and to not meet the exclusion criteria. After patients give written informed consent, the patient information required to check eligibility will be entered on the study registration form. Before the final registration, the researcher who entered the registration form data and the other co-researchers will double-check each other to confirm.

**6.4. Allocation method**

Not applicable

**6.5. Blinding and Key Opening**

Not applicable

**7. Treatment plan**

**7.1. Study protocol**

(1) An arterial catheter is inserted into the left radial artery of each patient after the induction of general anesthesia.

(2) The finger cuff of the ClearSight system is placed over the left middle phalanx of the third finger, ipsilateral to the radial artery catheter.

(3) The pulse oximeter probe is attached to an ipsilateral finger not competing with the finger cuff of the ClearSight.

(4) All devices are calibrated.

(5) The management of intraoperative anesthesia is left to the anesthesiologist in charge. A specific anesthesia protocol is not defined. The data reported by the ClearSight are not considered in the perioperative management of the patient.

(6) The management of the patient in the ICU is left to the doctor in charge. A specific management protocol is not defined. The data reported by the ClearSight are not considered in the ICU management of the patient.

**Data acquisition**

**ClearSight:**

Systolic arterial pressure (SAPcs), diastolic arterial pressure (DAPcs), mean arterial pressure (MAPcs), CO, SV, and SVV data are recorded at 20-second intervals.

**FloTrac** **(arterial catheter):**

SAP, DAP, MAP, CO, SV, and SVI data are recorded at 20-second intervals.

**Radical-7 pulse oximeter:**

PI and SpO_2_ data are recorded at 10-second intervals.

**Anesthetic monitor in the operating room and the ICU:**

Heart rate, body temperature, and central venous pressure data are recorded at 1-minute intervals.

The systolic, diastolic, and mean arterial pressures, and the CO, SV, and SVI data obtained using the ClearSight and the FloTrac are recorded at 20-second intervals, and a set of three consecutive data points (obtained over 1 minute) are averaged to yield one datum. The IAP, heart rate, and body temperature are recorded at 1-minute intervals and stored on an anesthesia monitor. PI values are recorded and stored at 10-second intervals on the pulse oximeter. The representative value of PI data obtained every minute are calculated by averaging six consecutive PI values. No manual description of measured values is required, because these data are automatically stored in these measuring devices.

**Other data:**

(1) Edema, body temperature, history of hypertension, and dose of the vasopressors.

(2) The damping coefficient and natural frequency of the transducer are checked by the fast-flush test (square wave test) 1 minute before each measurement period.

(3) Time of the occurrence of artifact for APcs and IAP. These data are used for extracting the artifacts.

(4) Time information: anesthesia time, each measuring period, starting time of the operation, time of the specimen extraction, time of the intestinal anastomosis, and finishing time of the operation.

**End of the study**

The end of the study for each patient is defined as 24 hours after the start of data measurement or 4 hours after entering the ICU, whichever comes first.

**7.2. Dose and schedule change criteria**

The ClearSight shuts down after 8 hours of continuous monitoring to prevent blood stasis of the finger. The finger cuff is moved to another finger if continuous measurements of 8 hours or more will be performed.

**7.3. Discontinuance of protocol**

(1) Cases that cannot be measured due to technical problems of the devices.

(2) Cases in which it is difficult to continue the protocol due to the occurrence of adverse events.

(3) Cases found to be ineligible after the inclusion.

(4) For other reasons, if the doctor in charge determines that data collection cannot be continued.

**7.4. Combined treatment or supportive care**

Not applicable

**7.5. Post treatment**

Not applicable

**8. Burden, risk, and benefit on the study subject. Evaluation and measures to minimize the burden and risk**

**8.1. Definition of adverse event**

Information on serious complications regarding the use of the ClearSight have not been reported from the manufacturer. The occurrence rate of serious complications is considered to be rare, because the ClearSight is used based on the recommendation by the manufacturer. However, adverse events are defined as follows, based on all possibilities:

If the anesthesiologist in charge determines that data collection cannot be continued because of severe blood stasis at the cuff attachment site during the study period.

Furthermore, adverse events in this study are defined as unknown events that occur in relation to this study. Known adverse events and symptoms or complications related to the underlying disease or surgery are not included as adverse events of the study.

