**8.2. Evaluate the adverse event**

Mild: No need for therapeutic intervention.

Severe: Immediate need for therapeutic intervention.

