**8.3. Expected adverse events**

Blood stasis, swelling, ischemia, skin discoloration, numbness, and ache of the finger at the cuff attachment site of the ClearSight.

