**12. Case report forms**

Case report data are reported on the form that includes the patient characteristic data, perioperative data, and case registration. The co-researcher will submit this form to the lead principal investigator after completing the form.

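### Section 8.1's definition of an adverse event conflicts with 8.2 and 8.3, so cuff-site finger harm may be under-reported or recorded inconsistently

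*Protocol*

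**What the plan says.** Section 8.1 of the Protocol gives the definition in two limbs and an exclusion.

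- **First limb.** An adverse event exists if the anesthesiologist in charge judges that "data collection cannot be continued because of severe blood stasis at the cuff attachment site during the study period".
- **Second limb.** In addition, "adverse events in this study are defined as unknown events that occur in relation to this study".
- **Exclusion.** "Known adverse events and symptoms or complications related to the underlying disease or surgery are not included as adverse events of the study".

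Section 8.2 grades events in two levels, the lower being "Mild: No need for therapeutic intervention".

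Section 8.3, headed as the list of expected adverse events, reads: "Blood stasis, swelling, ischemia, skin discoloration, numbness, and ache of the finger at the cuff attachment site of the ClearSight".

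Section 7.3(2) uses the term as a ground for discontinuation: "Cases in which it is difficult to continue the protocol due to the occurrence of adverse events". Section 7.3(4) adds a separate ground that leaves the decision to the doctor in charge.

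On data capture, section 12 says: "Case report data are reported on the form that includes the patient characteristic data, perioperative data, and case registration".

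**The concern.** The events that 8.3 calls adverse events are, for the most part, not adverse events under 8.1. A reader who applies 8.1 would not count a numb or discolored finger. A reader who starts from 8.3 and 8.2 would count it and grade it mild.

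This matters because of where the study's own physical risk lies. Sections 2.1 and 2.2 say that the arterial catheter and the FloTrac are used in these patients anyway, and section 3 calls the pulse oximeter standard equipment. The ClearSight cuff is what participation adds, so the finger under the cuff is the main place where the study itself could cause physical harm. The protocol acknowledges this risk: section 7.2 describes an automatic shutdown after 8 hours to prevent stasis, and section 9.1 allows participation of up to 24 hours. At stake is whether the study can state reliably how often the cuff injured a finger.

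**Working it through.** No arithmetic beyond a count applies, and the protocol gives no figure to reproduce. The check applies each limb of 8.1, as written, to each event in 8.3.

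| Event listed in 8.3 | First limb of 8.1 (severe stasis that ends data collection) | Second limb of 8.1 (unknown, study-related) | Counted under 8.1? |
|---|---|---|---|
| Blood stasis | Only if severe and data collection is judged unable to continue | No, listed in advance | Only in that case |
| Swelling | No | No, listed in advance | No |
| Ischemia | No | No, listed in advance | No |
| Skin discoloration | No | No, listed in advance | No |
| Numbness | No | No, listed in advance | No |
| Ache | No | No, listed in advance | No |

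Result: 5 of 6 listed events meet neither limb. The sixth meets the definition only in its most severe form.

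**Against 8.2.** The mild grade covers events that need no treatment. Among the events in 8.3, the literal definition leaves at most one candidate for that grade: stasis bad enough to stop data collection but not needing treatment. Events that really were unforeseen could still be graded mild.

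**Is there another route by which the events are captured?**

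- Section 7.1, under other data, lists edema but no inspection of the cuff site.
- Section 9.2 lists patient characteristics, device readings, the fast-flush test, times, artifacts and vasopressors. No finger check appears.
- Section 12 names three kinds of content for the case report form, and adverse events are not among them.
- Sections 13 and 22 mark the safety committee, monitoring and audit as not applicable.

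The definition in 8.1 is therefore the main stated basis for deciding what counts as harm, and it disagrees with the two sections that follow it.

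**The case against.** The strongest reply is that 8.1 should not be read alone. The heading of 8.3 itself calls the finger events adverse events, and 8.2 grades events that need no treatment. Taken together, the three sections can be read as meaning that these events do count. The exclusion sentence is also ambiguous: its closing reference to disease or surgery may qualify the known adverse events as well, in which case that sentence would not exclude known effects of the cuff.

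Part of this stands. It is not certain that the five events would go uncounted, only that the text leaves it unclear. The ambiguity of the exclusion does not remove the conflict, because the sentence before it already restricts the second limb to unknown events.

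A reader might also infer three stronger conclusions, which the documents do not support.

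- **That patients could not be withdrawn for a finger injury.** Section 7.3(2) concerns events that make continuing difficult, which is close to the first limb of 8.1. Section 7.3(4) lets the doctor in charge stop data collection for other reasons, whatever the event is called.
- **That the study would report almost no adverse events whatever happened.** Unforeseen study-related events still count, and staff working from 8.3 may record the listed ones.
- **That the study's results are compromised.** No endpoint in section 10 and no analysis in section 11.3 concerns safety.

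The protocol also describes the device as approved for daily practice (17.3) and used as its manufacturer recommends (8.1). That bears on how often harm is expected. It does not bear on whether harm is recorded consistently.

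**Conclusion.** The inconsistency is real and should be corrected. On its literal wording, 8.1 excludes five of the six cuff-site events that 8.3 lists, and all stasis that does not stop data collection. It therefore conflicts with 8.2 and 8.3. The likely consequence is under-reporting or uneven recording of harm from the device that the study adds. How many events would be lost cannot be estimated, because the protocol gives no expected rate for any of them.

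The conclusion rests on two readings: that an event named in 8.3 is not unknown in the sense of 8.1, and that no adverse event item exists on the case report form or recording sheet beyond what sections 9.2 and 12 describe. If the actual forms carry such an item, the practical effect is smaller, but the text of 8.1 still needs reconciling. The ability to stop the protocol, the primary endpoint and the sample size are not affected.

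**What to change.** Reconcile 8.1 with 8.2 and 8.3 in three steps.

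1. State in 8.1 that every cuff-site event listed in 8.3 is recorded as an adverse event and graded by 8.2, whether or not data collection continues. Keep unforeseen study-related events as a further category.
2. Word the exclusion so that it covers only events attributable to the underlying disease or surgery.
3. Add one line for cuff-site events to the recording sheet that staff in the operating room and ICU already complete under 9.2.

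This changes what is recorded and sets no rule for clinical management. The cost is a sentence or two of text and one line on a form, plus the ethics committee handling that section 18 requires for the change. The downside is a higher reported event count, which should be presented as the result of fuller recording.
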